**Figure 3 figure3:**
[figure not shown]
Member home page for arm 1.

**Figure 4 figure4:**
[figure not shown]
Member home page for arm 2.

**Figure 5 figure5:**
[figure not shown]
Member home page for arm 3.

### Data Collection

Evolution Health developed a custom data collection interface and reporting mechanism. Data will be collected for each member who is randomized into the experiment. Data on age and gender will be collected at registration or at secure sign-on in various white-label versions. The course components that will be promoted by the tips and to-do items are listed in Table 4.

The following behaviors are tracked in the custom database for each tip and to-do item that is randomly presented to a user: whether a tip was shown, whether a tip was clicked on, and whether a user completed the course component described in a tip or to-do item.

It is possible for a single member to participate in both courses. However, the study was designed to test behavioral economics prompts, not courses. Participants will be randomized to an intervention arm in which behavioral nudges and prompts are consistent across courses.

**Table 4 table4:** Course components tracked for engagement.

Action code	Course component
1^a^	Uploading a personal image to their profile
2^a^	Completing cognitive behavioral therapy session 1
3^a^	Use of the program’s diary
4^a^	Read a community post
5	Review another member’s profile
6	Posting in the community
7^a^	Review a course worksheet
8^a^	Set personal goals
9	Read other members’ goals
10^a^	Complete the depression and anxiety test
11^a^	Watch the *Getting Started* video
12	Give a community member a thumbs-up
13	Encourage a community member by clicking their “show support” icon
14	Private message a community moderator

^a^Item in the to-do checklist.

### Primary Outcome: Engagement With Tips and To-do Items

We will first measure engagement with the tips and to-do items in arms 2 and 3. We will compare the frequency of engagement with each nudge and behavioral prompt by age and gender. A member’s engagement with tips will be measured as the proportion of tips that were clicked. Specifically, it will be a value between 0 and 1, calculated as the number of tips that a member clicked divided by the number of tips that were presented to the member. Engagement with to-do items will be measured as the number of to-do items that a member clicked, and course component completion rates will be measured as the number of course components that a member completed. All comparisons between arms 2 and 3 will be conducted by using an independent sample 1-tailed *t* test; a conventional α level (.05) for statistical significance will be used.

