### Power and Sample Size

Our goal is to obtain 0.95 power to detect a significant difference in the proportion of users who complete at least 1 cognitive behavioral therapy session between the two treatment groups (arm 2 vs arm 3). Based on a preliminary analysis of an early subsample of users from November 1 to December 9, 2021 (arm 1: n=510; power=3.14%; arm 2: n=484; power=5.79%) and a conventional α level (.05) for statistical significance, we would require a sample of 4224 users, with 1414 users in each treatment group. Multimedia Appendix 1 shows our study’s CONSORT-EHEALTH (Consolidated Standards of Reporting Trials of Electronic and Mobile Health Applications and Online Telehealth) checklist [50].

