## Discussion

### Hypotheses

We hypothesize that members will engage with the prompts and nudges. We also hypothesize that the secondary results will generate insights on the types of prompts and nudges that are the most likely to result in engagement among members. This finding may be important, as dose-response relationships have been observed in digital health interventions [8,51].

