### Practical Implications

If we learn that the prompts are used by members, the arm 2 or arm 3 home page will become the default user home page for all new and existing members.

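### The primary-outcome t tests of arm 2 against arm 3 are one-tailed at .05, but no direction is stated and the plan leaves either arm as the possible better one

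*Protocol article*

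**What the plan says.** The Primary Outcome section of the protocol article defines three measures: the proportion of presented tips that a member clicked, the number of to-do items clicked, and the number of course components completed. It then fixes the test: "All comparisons between arms 2 and 3 will be conducted by using an independent sample 1-tailed". The test named is the t test, and the section adds that "a conventional α level (.05) for statistical significance will be used".

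Four other sections bear on direction:

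- **Power and Sample Size:** the aim is stated as "Our goal is to obtain 0.95 power to detect a significant difference in the proportion of users who complete at least 1 cognitive behavioral therapy". The endpoint is thus one such session or more, and the contrast is arm 2 against arm 3. The inputs are printed as "arm 1: n=510; power=3.14%; arm 2: n=484; power=5.79" (per cent). From these the article derives a total of 4224 and a group size of 1414 at α = .05. Sidedness is not given there.
- **Hypotheses:** "We hypothesize that members will engage with the prompts and nudges". Nothing ranks arm 3 against arm 2.
- **Practical Implications:** if the prompts are used, "the arm 2 or arm 3 home page will become the default user home page".
- **Secondary and Tertiary Outcomes:** component completion and tip engagement in arms 2 and 3 are analysed by 1-way ANOVA with tip type as the factor, followed by regression.

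**The concern.** A one-tailed test is not defined until the favoured direction is named. The article chooses the one-tailed test but names no direction, and its own wording elsewhere is open: a difference in the power section, which tip type is most engaging in the tertiary outcome, and either page as the eventual default.

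Nor is the direction self-evident. Arm 3 has different tip content and also a checklist, and Table 4 marks 8 of the 14 tracked components as checklist items. The checklist could raise completion while giving members another route to the same components, and so draw clicks away from tips. That mechanism is a conjecture, but it shows that the two measures need not move the same way.

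At stake is either the stated error rate of the primary comparisons or their ability to report one of the two possible results.

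**Working it through.** **1. Which measures are affected.** Under Intervention Groups, only arm 3 has a to-do checklist, so to-do clicks cannot be compared between arms. That leaves tip-click proportion and number of components completed.

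**2. Is a direction given elsewhere?** The Objective and the Secondary Outcomes section speak of increases, but of prompts raising engagement, not of one prompted arm over the other. The Hypotheses section says only that members will engage. No section supplies the direction.

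**3. Error rate if the tail is chosen after the data.** The effective rule is to reject when |z| > 1.645. Under no difference, P = 2 × 0.05 = 0.10, against the stated .05, per comparison.

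**4. Consequence if the tail is fixed and the truth is opposite.** Take the planned difference, reversed, with n = 1414 per group:

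- SE = √[(0.0314×0.9686 + 0.0579×0.9421)/1414] = 0.2915/37.60 = 0.00775
- d/SE = 0.0265/0.00775 = 3.42
- P(significant in the fixed direction) = Φ(−3.42 − 1.645) ≈ 2×10⁻⁷

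The better arm could not be declared better by such a test.

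**5. The plan's own sample size.** Inputs are from Power and Sample Size. The two percentages are printed as power and labelled arm 1 and arm 2. They agree with 16/510 = 3.14% and 28/484 = 5.79%, so I read them as completion proportions and assume that they serve as the planning rates for arm 2 against arm 3, with 1:1 allocation. With d = 0.0265 and p̄ = 0.04465:

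n = [z_α√(2p̄(1−p̄)) + z_β√(p₁q₁+p₂q₂)]² / d², where √(2p̄(1−p̄)) = 0.2921, √(p₁q₁+p₂q₂) = 0.2915 and z_β = 1.645.

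- One-sided: (1.645×0.2921 + 1.645×0.2915)²/0.0265² → 1313
- Two-sided: (1.960×0.2921 + 1.645×0.2915)²/0.0265² → 1576

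The continuity-corrected n is (n/4)[1 + √(1 + 4/(nd))]², which gives 1387 one-sided and 1651 two-sided. The arcsine method gives 1286 and 1544. The closest to 1414 is 1387, which is 27/1414 = 1.9% lower. It is not an exact match. The other results are further away: 1313 and 1286 are lower, and every two-sided figure is 1544 or more.

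**6. Power at 1414 per group.** Power = Φ{[d√n − z_α×0.2921]/0.2915}, with d√n = 0.9965.

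| Method | One-sided .05 | Two-sided .05 |
|---|---|---|
| Uncorrected | Φ(1.770) = 96.2% | Φ(1.455) = 92.7% |
| Continuity-corrected | 95.3% | 91.4% |
| Fisher exact (.025 per tail if two-sided) | 95.7% | 91.9% |

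The printed total of 4224 would mean 4224/3 = 1408 per group rather than 1414 (3 × 1414 = 4242). Uncorrected power at 1408 is 96.1% and 92.6%, so nothing here turns on that discrepancy.

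**The case against.** The strongest reply is that a one-sided test with a direction fixed in advance is valid at .05, that being unable to declare the opposite result is its ordinary property, and that a separate analysis plan could name the direction. The build-up of the arms, from no prompts to tips to tips plus a checklist, hints at arm 3 being higher on completion. This stands as far as it goes, but the article never says so, and the hint does not carry over to tip clicks.

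A reader might also infer four stronger things that the text does not support:

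- **That every arm 2 against arm 3 test is one-tailed.** The primary-outcome sentence says all comparisons, but the next two sections prescribe ANOVA, which has no direction. An arm 2 advantage could show there, because directive tips appear only in arm 2. The one-tailed limitation belongs to the primary t tests, and the sentence conflicts with those later sections.
- **That the error rate is 10%.** It is .10 only if the tail is picked after the data are seen, and nothing says that it will be.
- **That the rollout choice rests on the t test.** Practical Implications makes it conditional on the prompts being used and does not say how the arm will be chosen. It shows only that both arms are live options.
- **That two-sided testing is free.** On the planning rates it misses the stated 0.95 goal.

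**Conclusion.** The point holds for the primary-outcome t tests on tip-click proportion and number of components completed. They are one-tailed at .05 with no direction, in a plan whose question and use are open in both directions. The size is conditional: type I error of .10 per comparison if the tail is chosen after the data, or no means of declaring one arm better by these tests if the tail is fixed.

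The nearest reproduction of 1414 suggests a one-sided calculation, but the match is approximate and the power section does not state sidedness. The power figures assume that 3.14% and 5.79% are completion proportions applicable to arm 2 against arm 3. They describe the two-proportion endpoint of at least 1 therapy session and say nothing direct about the power of the t tests.

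**What to change.** In the Primary Outcome section, replace the one-tailed sentence with, for example: *For tip-click proportion and number of components completed, arms 2 and 3 will be compared by two-sided independent-samples t tests at α = .05, with 95% confidence intervals for the difference.* This also removes the clash of direction with the ANOVAs.

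In Power and Sample Size, restate the power for a two-sided test: about 93% (91% to 93% by method) at 1414 per group, with the two percentages labelled as completion proportions and the arms they come from made clear.

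The cost is two text changes and no added enrolment. On the uncorrected calculation, power falls from 96.2% to 92.7%, which is 3.5 points, and ends below the 0.95 goal. Reaching 0.95 two-sided would take about 1576 to 1651 per group. The Results section says that the requirement was exceeded in every arm but gives no numbers, so power at the achieved size cannot be stated.

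The alternative is to name and justify a direction for each measure. With data collection finished in May 2022 and an early subsample already analysed, it would be hard to show that such a choice was made independently of the data, so two-sided testing is the safer repair.

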### Randomization

During the registration process, by using a random number generator, new members will be assigned into 1 of the 3 arms (Figure 2). Randomization will be conducted by using simple randomization.

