### Strengths and Limitations

A strength of this experiment is that it will be conducted in an ad libitum environment. Unlike most digital health studies, ours will not be conducted with a small population in a controlled environment. Further, members will not be aware of the experiment, which will limit participant bias and the Hawthorne effect.

A limitation of this experiment is that, especially due to the anonymity of members, we have no way of knowing who members are. We have no way of knowing whether registrants are people with depression or anxiety who are seeking help, or are browsing for other reasons. However, we have exceeded sample size requirements and believe that the large number of subjects should dampen these effects on the results.

A final limitation is that not all white-label clients license all course components. For example, some community tools and the depression and anxiety test are feature flags that are not used by all white-label clients. As the primary purpose of this experiment is to test whether members engage with prompts and nudges, we do not expect this particular limitation to hamper the overall results.

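### The arm 2 versus arm 3 t tests make no use of age and gender, which are collected anyway; adjusting for them is an optional and probably small gain in precision, not a validity repair

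*Protocol article*

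**What the plan says.** All places are in the protocol article.

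- **Randomization:** "Randomization will be conducted by using simple randomization". No stratification factor is named.
- **Primary Outcome:** "All comparisons between arms 2 and 3 will be conducted by using an independent sample 1-tailed" t test, and "a conventional α level (.05) for statistical significance will be used". No covariate is named for the arm contrast. The same section breaks engagement down by age and gender.
- **Data Collection:** "Data on age and gender will be collected at registration or at secure sign-on in various white-label versions". Secure sign-on appears here as a point at which age and gender are obtained, not as a variable in its own right.
- **Secondary Outcomes and Tertiary Outcomes:** a one-way ANOVA with tip type as the factor, then a regression asking whether age and gender predict which tip type engages most.
- **Strengths and Limitations:** "not all white-label clients license all course components". Some community tools and the depression and anxiety test are given as examples.

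**The concern.** The test is named and applied to every arm 2 versus arm 3 comparison, so this is a stated choice and not a detail left to an unseen analysis plan. The authors already hold age and gender, and already intend to fit regressions with them. Yet the between-arm test leaves any variation that these two variables explain in the error term.

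If age and gender, or the client through which a member joined, are related to clicking and completion, the intervals and p-values for the arm difference are somewhat wider than they need to be. Data collection has ended, so stratified allocation is no longer possible. Adjustment in the analysis is the remaining way to gain that precision.

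**Working it through.** **1. The plan's own figure.** The section on power gives 0.95 power, alpha .05, planning values printed as "arm 1: n=510; power=3.14%; arm 2: n=484; power=5.79"% and the result "we would require a sample of 4224 users, with 1414 users in each treatment group". The two percentages are read here as completion proportions (16/510 = 3.14%, 28/484 = 5.79%).

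- Mean proportion: (0.0314 + 0.0579)/2 = 0.04465. Difference: 0.0265. One-sided z for .05 and z for 0.95 power: both 1.645.
- n = [1.645·√(2 × 0.04465 × 0.95535) + 1.645·√(0.0314 × 0.9686 + 0.0579 × 0.9421)]² / 0.0265², which rounds up to 1313.
- With continuity correction: (n/4)·[1 + √(1 + 4/(n × 0.0265))]² gives 1387, which is 1.9% below 1414.
- The two-sided versions give 1576 and 1651.

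The stated size therefore fits a one-sided test best, and one-sided critical values are used below with n = 1414 per arm.

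**2. Gain from adjustment.** Let R² be the share of outcome variance explained by the baseline variables. The documents give no value, so a range is assumed.

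- Standard error ratio = √(1 − R²).
- Equivalent n per arm = 1414 × (1 − R²).
- Power = Φ[(1.645 + z)/√(1 − R²) − 1.645], where z is 0.842 for an unadjusted power of 0.80 and 1.645 for 0.95.

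| R² | SE reduction | Equivalent n per arm | 0.80 becomes | 0.95 becomes |
|---|---|---|---|---|
| 0.02 | 1.0% | 1386 | 0.807 | 0.953 |
| 0.05 | 2.5% | 1344 | 0.818 | 0.958 |
| 0.10 | 5.1% | 1273 | 0.836 | 0.966 |

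Both starting powers are shown because the 0.95 target is set for a completion proportion, and the article states no power for the t-test outcomes.

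**3. How large R² could be for gender.** Take the completion outcome at about 4.5% overall and an assumed 50/50 gender split.

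- Completion of 3% against 6%: R² = 0.015²/(0.045 × 0.955) = 0.5%.
- The extreme of 0% against 9%: R² = 0.045²/(0.045 × 0.955) = 4.7%.

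For a rare binary outcome, gender alone is therefore near or below the bottom of the table. The click proportions and component counts could behave differently, but no figure is given for them.

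**4. Chance imbalance.** The SD of a standardised baseline difference between two arms of 1414 is √(2/1414) = 0.038. A 50% characteristic differs with SD √(2 × 0.25/1414) = 1.9 percentage points (95% range about ±3.7). An imbalance of 1.96 SD shifts the estimate by 1.96 × 0.0376 × √R², which is 0.010 outcome SD at R² = 0.02 and 0.023 at R² = 0.10. The unadjusted standard error is 0.038 outcome SD.

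**5. Simulation.** 2828 members were allocated by simple randomisation, with a normal outcome and 4000 runs per setting.

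- R² = 0.02: one-sided null rejection 0.049 unadjusted and 0.052 adjusted; power 0.796 and 0.803.
- R² = 0.10: null rejection 0.052 and 0.051; power 0.783 and 0.822.
- With no true effect, the mean unadjusted estimate was 0.000.

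Monte Carlo error is about 0.003 for null rejection and √(0.8 × 0.2/4000) = 0.006 for power. The gain at 0.02 is thus within noise, and the gain at 0.10 is not.

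**The case against.** The case for leaving the plan alone is substantial, and most of it stands.

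- **Validity.** A reader might infer that chance imbalance in gender, age or client mix biases the arm effect. It does not. Under simple randomisation the t test is unbiased, and its standard error already allows for chance imbalance. That imbalance is the same small precision effect seen from another side, not a second harm.
- **Sign-on route.** A reader might infer that the route (free-to-consumer or white-label) is a recorded baseline variable. The article names sign-on only as a point of collection. White-label client is the most plausible strong covariate, because it limits which components a member can complete, but its availability is an inference.
- **Size.** No R-squared is given. At the plan's 0.95 target the gain is 0.3 to 1.6 percentage points of power over the assumed range, and the article reports that the required sample was exceeded in each arm.
- **Expectation.** The plan asks whether age and gender matter. It does not claim that they are strongly prognostic.
- **The secondary ANOVA.** Its factor is tip type, and arm 3 contains two types. A model on arm would merge social proof and present bias tips and answer a different question.
- **Timing.** Collection ended in May 2022, and early rates had been examined by arm, labelled as arms 1 and 2. Changing the primary test is therefore a change made after data exist.

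These points narrow the proposal to age and gender by default and to the primary comparison only. They do not remove it: the variables are in hand, and the adjusted analysis kept its error rate in simulation.

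**Conclusion.** The point holds as an optional efficiency improvement. The article fixes an unadjusted test for every arm 2 versus arm 3 comparison, although age and gender are available. The cost of that choice is precision alone: about 1% to 5% of the standard error if R-squared lies between 0.02 and 0.10, and probably nearer the low end for age and gender by themselves. A gain toward the upper end would most plausibly need white-label client to be both recorded and prognostic, and the article establishes neither. The documents do not support calling the planned test biased or invalid. The figures assume 1414 per arm, a one-sided .05 test and the stated range of R-squared.

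**What to change.** In the section on the primary outcome, before arms 2 and 3 are compared:

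- Replace the t test with a linear model of each outcome compared between the two arms, on arm, age and gender, with robust standard errors.
- Add white-label client, or free-to-consumer versus white-label, only if it is recorded at registration.
- Give missing age or gender a 'not recorded' category, with age in bands for this purpose, so that no member is dropped.
- Report the adjusted arm difference as the main result and the unadjusted t test as a sensitivity analysis.

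In the section on secondary outcomes, keep tip type as the factor and do not replace it with arm.

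The cost is a change of wording and a few lines of code, with no new data and no further members. The change should be dated, with a statement that arms 2 and 3 have not yet been compared. If they have been, the published t test should remain the main analysis and the adjusted model should be labelled post hoc.

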### Secondary Outcomes: Completion of Course Components

A secondary outcome of this experiment is to test whether the presentation of tips and to-do items increases the overall completion of course content. We will achieve this by comparing course component completion rates in arm 2 and arm 3 via a 1-way ANOVA in which the types of tips are used as the independent variable. We will then assess if age and gender predict which type of tip is the most engaging by using multiple regression.

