**Methods:**

New members who register for the self-guided anxiety and depression courses on the Evolution Health platform will be randomized into 1 of 3 arms. The first control arm will feature a member home page without any behavioral nudges or prompts. The second arm will feature a member home page with a *Tip-of-the-Day* section containing directive content. Arm 3 will feature a member home page with a *Tip-of-the-Day* section containing social proof and present bias content. The third arm will also feature a to-do item checklist.

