### Objective

The main objective of our 3-arm randomized controlled trial is to test whether registered members in two well-established, self-guided digital health courses for anxiety and depression will engage with four different types of nudges and prompts, and whether engaging with nudges and prompts increases engagement within the courses.

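### The completion analysis compares only the two nudge arms, so it cannot show whether nudges increase course completion over no nudges

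*Protocol article*

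**What the plan says.** The abstract's Methods paragraph defines arm 1 as the control: "The first control arm will feature a member home page without any behavioral nudges or prompts". Under Intervention Groups, arm 2 shows directive tips, and arm 3 shows social proof and present bias tips plus a to-do checklist.

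The Objective section makes within-course engagement part of the main objective: "whether engaging with nudges and prompts increases engagement within the courses". The section on completion of course components turns this into a secondary outcome, to "test whether the presentation of tips and to-do items increases the overall completion of course content". The next sentence gives the method: "We will achieve this by comparing course component completion rates in arm 2 and arm 3 via a 1-way ANOVA". The factor in that analysis is the type of tip; the types listed under Tertiary Outcomes are directive, social proof and present bias.

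The power goal is also set for arm 2 against arm 3. The abstract's Results paragraph promises to examine whether nudges lead to higher completion, but names no arm and no test.

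**The concern.** The question and the test, in consecutive sentences, do not match. Whether presenting nudges increases completion is a question about nudges against none, and the only group without nudges is arm 1. The analysis leaves that group out, and its factor, type of tip, has no level for no tip.

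A null result between arms 2 and 3 would look the same whether both home pages doubled completion or neither did anything. A positive result would show only that one package does better than the other.

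The objective adds a second difficulty. It speaks of the effect of engaging with nudges, which members choose after randomisation and which motivation is likely to confound. A contrast with arm 1 by assigned arm avoids that problem, but none is planned.

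**Working it through.** **1. Which arms each section compares**

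| Section | Outcome | Arms | Can arm 1 contribute? |
|---|---|---|---|
| Power and Sample Size | at least 1 therapy session completed | 2 vs 3 | yes |
| Primary Outcome | tip and to-do engagement | 2 vs 3 | no, it is shown none |
| Secondary Outcomes | course component completion | 2 vs 3 | yes |
| Tertiary Outcomes | engagement by type of tip | 2 vs 3 | no, it is shown none |

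The mismatch therefore lies in the completion analysis. No section names a comparison with arm 1.

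**2. Inputs for the size of the problem**

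All come from Power and Sample Size: arm 1, n=510, 3.14%; arm 2, n=484, 5.79%; α .05; power goal 0.95; 1414 per group; total 4224. The two percentages are printed under the label power. They match 16/510 = 3.14% and 28/484 = 5.79%, so I read them as proportions completing at least 1 session. The counts are back-calculated.

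**3. The plan's own sample size**

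n = [z_α√(2p̄(1−p̄)) + z_β√(p₁(1−p₁)+p₂(1−p₂))]² / (p₂−p₁)², with p₁ = 0.0314, p₂ = 0.0579 and p̄ = 0.04465. The two square roots are 0.2921 and 0.2915.

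- One-sided .05, power 0.95: 1313 per group, or 1387 with continuity correction.
- Two-sided .05, power 0.95: 1576, or 1651 corrected.

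The nearest to 1414 is the one-sided corrected figure, 1.9% lower, so the plan's figure is approximately but not exactly reproduced. The total is slightly off (3 × 1414 = 4242; 4224/3 = 1408), but nothing below depends on that.

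**4. The early difference between arms 1 and 2**

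Difference = 0.0579 − 0.0314 = 0.0265. Standard error = √(0.0314×0.9686/510 + 0.0579×0.9421/484) = 0.0131. The 95% CI is 0.0265 ± 1.96×0.0131, which with the unrounded counts gives 0.08 to 5.22 points. The ratio is 5.79/3.14 = 1.84. The chi-square p-value is 0.042 uncorrected and 0.061 with continuity correction, so the evidence is borderline.

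**5. What each contrast would detect**

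Suppose arm 1 is at 3.14% and arms 2 and 3 are both at 5.79%.

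- *Arm 2 vs arm 3:* the true difference is zero, so the rejection rate is the type I error. In 20,000 simulated trials (1408 per arm) it was 5.1% one-sided and 4.9% two-sided.
- *Arm 2 vs arm 1 alone, 1414 per arm, two-sided .05:* Φ[(0.0265 − 1.96×0.00777)/0.00775] = Φ(1.45) = 92.7%, where 0.00777 = 0.2921/√1414 and 0.00775 = 0.2915/√1414.
- *Arm 2 vs arm 1, required to follow a significant global 3-arm test:* about 91 to 92% by simulation, or about 87 to 88% if arm 3 lies midway between the other two.

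**The case against.** Several points in the plan's defence stand.

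- **Scope.** A reader might infer that leaving arm 1 out of every comparison is an error throughout. It is not: arm 1 sees no tips or to-do items, so it has no value on those engagement measures. The primary outcome states its own scope: "We will first measure engagement with the tips and to-do items in arms 2 and 3".
- **Importance.** Completion is labelled secondary, and Strengths and Limitations says the primary purpose is to learn whether members engage with the prompts. It would be too strong to say that the trial's principal question goes untested. But within-course engagement is in the main objective, and the power goal rests on a completion measure, so the gap still matters.
- **Data.** Data Collection says "The following behaviors are tracked in the custom database for each tip and to-do item that is randomly presented to a user". A reader might infer that arm 1 has no completion data. The same section says data are collected for every randomised member, and an arm 1 figure appears in the sample-size section, so that reading is not supported.
- **Rollout.** Practical Implications says that, if members use the prompts, "the arm 2 or arm 3 home page will become the default user home page". This does not require beating arm 1, but it is a product decision in line with the stated primary purpose, not a statistical error.
- **The figures.** The sample-size paragraph labels its rates arms 1 and 2 while naming arm 2 against arm 3 as its contrast. If the labels are wrong, the 2.65 points are not a control-versus-nudge difference. The figures also concern the at-least-1-session proportion, not the number of components completed.

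A fuller protocol or analysis plan might add the missing contrast. But the article does not leave the comparison open: it names one that cannot answer its question, and a plan that followed it would inherit the fault.

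**Conclusion.** The completion analysis is wrong as written. It can show a difference between two nudge packages; it cannot show that presenting nudges increases completion. That conclusion comes from the text alone and needs no figures.

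Its size is conditional on the printed arm labels and on reading the percentages as proportions completing at least 1 session. On that basis, a rise from 3.14% to 5.79% shared by both nudge arms would be flagged by the planned contrast about 5% of the time, against about 92.7% for a direct arm 2 vs arm 1 test at 1414 per arm. The early difference is too fragile to establish that nudges work, and the documents do not support reading it that way. No power can be given for the component count, because no variance is stated.

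**What to change.** In Secondary Outcomes, compare course component completion by randomised arm across all three arms, with all randomised members included. Run a global 3-arm test at .05 and, if it is significant, the contrasts arm 2 vs 1, arm 3 vs 1 and arm 3 vs 2, each at two-sided .05. With exactly three arms this order holds the family-wise error at .05. Count completions the same way in every arm, whether or not a tip or item was shown, and allow for components that some white-label clients do not license. Reword the objective as the effect of being assigned nudges.

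Date the change and disclose that a subsample from November 1 to December 9, 2021 had already been inspected. Correct the labels in the sample-size paragraph and restate the power for the control contrast.

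**Cost.** No new arm or data collection is needed: arm 1 is already randomised, and collection ended in May 2022. The price is power somewhat below the 0.95 goal at the planned size. A stand-alone two-sided test would need 1576 per arm to reach 0.95. The article says the requirement was exceeded but not by how much, so the shortfall may be smaller in practice.
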